## Abstract

**Background:**

Physical activity (PA) is beneficial to people’s physical and psychological health. Physically active children are likely to become active adults; thus, active lifestyles should be promoted from childhood. Parents are crucial for shaping their children’s behaviors, but many lack the knowledge and skills to provide optimal support for PA. The “Active 1 + FUN” intervention was designed to enhance PA of the whole family, and improve parenting methods of both fathers and mothers.

**Methods:**

“Active 1 + FUN” is a family-based intervention designed using the tenets of self-determination theory. The intervention was designed to help parents support their children’s basic psychological needs for competence (by providing informational feedback and optimal challenges), autonomy (by exploring a variety of activities and reducing controlling behaviors), and relatedness (by increasing co-PA between parents and child). The intervention components include interactive workshops, activity sessions, physical activity homework, activity planning consultations, easy sports equipment, and online materials. A randomized controlled trial will be conducted to evaluate the intervention. A target sample of 204 Primary three to five students (8 to 11 years) and their parents will be randomly allocated to the experimental group or a wait-list control group. The experimental group will receive a ten-session intervention which spans approximately six months. The control group will receive intervention one year later. Children’s accelerometer-based leisure-time physical activity (primary outcome) and secondary outcomes will be assessed at baseline, at end of intervention period (6 months after baseline), and at follow-up (12 months after baseline). Qualitative interviews will be conducted to determine effective intervention components from the perspective of children and parents. We hypothesize that the intervention will increase parents’ and children’s activity behaviors and that children will experience higher levels of needs satisfaction with regard to physical activity participation.

**Discussion:**

Physical activity interventions often target children only, but ones that also involve parents may be more beneficial. The “Active 1 + FUN” intervention will be organized and delivered by trained trainers. Consequently, this intervention could be scaled to a larger number of Hong Kong schools in the future and could impact a wider population of schoolchildren.

**Trial registration:**

ANZCTR ACTRN12618001524280. Registered 11 September 2018.

## Background

Physical activity is related to better physical and psychological health outcomes across the lifespan. The benefits of physical activity include low blood lipids, low prevalence of overweight and obesity, high bone mineral density, and few symptoms of depression [1, 2]. Researchers have also found that physical activity behaviors or habits track from childhood to adulthood [3]. Essentially, physically active children and adolescents will likely to be physically active during adulthood. Recent research also suggests that physical activity may improve children’s cognitive functions [4, 5] and academic performance at school [6]. Therefore, it is important to ensure that young people are engaging in sufficient levels of physical activity to support their current and future health status.

The development of competency in a range of fundamental movement skills (FMS) during childhood may help to establish a lifelong commitment to physical activity [7]. FMS include locomotor (e.g., running and jumping), object-control (e.g., throwing and catching) and stability (e.g., balancing and twisting) skills, which are regarded as the “building blocks” for movement and the foundation for participation in sports and physical activities [8, 9]. FMS competency of among schoolchildren is positively associated with various health benefits, namely, greater engagement of physical activity, greater cardiorespiratory endurance, higher self-esteem, and lower risks of overweight and obesity [10, 11]. As such, improving primary schoolchildren’s FMS may increase their engagement in physical activity and enable them to live an active and healthy lifestyle throughout their lifespans.

### Inactivity in children: The Hong Kong context

The World Health Organization [12] has recommended that children engage in at least 60 min of moderate-to-vigorous physical activity (MVPA) daily. Despite the known benefits of physical activity, the majority (85 to 90%) of the children in Hong Kong do not meet these recommended levels of physical activity [13, 14]. In response, school-based interventions have been designed and evaluated in Hong Kong to increase students’ physical activity levels during the school day, including physical education lessons [15]. However, few school-based interventions were not designed to enhance MVPA in the after school period or during weekends (e.g., [16]). Interventions involving parents may help to increase children’s physical activity during these time periods by expanding and extending opportunities to be active (e.g., [17, 18]).

### Children’s physical activity habits and parental influence

Children’s physical activity habits are shaped by their parents. This is particularly true for younger children who, compared with adolescents, require more care and spend more time with their parents. Parents typically act as the primary socialization agents in young children’s lives. Not surprisingly, researchers have found positive associations between parents’ and their children’s physical activity levels [13, 19, 20]. A meta-analysis conducted by Yao and Rhodes [21] found that support from parents and their modelling behaviors were related to children’s physical activity. Further, researchers have found that increases in joint parent-child physical activity may also be an effective method for increasing activity levels of both parents and children [22].

When compared to Australian parents, Hong Kong children report significantly lower levels of parental support for physical activity [13]. This may be due to Hong Kong parents’ lack of knowledge, or the diminished value they place on physical activity due to the relative importance of children’s academic achievement [23]. Contrary to these parents’ beliefs, researchers have shown that restricting children’s physical activity may be counterproductive to their academic performances [24]. For instance, researchers found that physical activity may improve children’s cognitive function [4, 5, 25] and academic performances [6]. Therefore, physical activity promotion programs in Hong Kong should involve parents, and educated them in or reinforce their understanding of the benefits of physical activity for their children’s cognitive and academic performance.

Parents and their children spend large portions of their time together in Hong Kong, especially during weekends. As such, there are ample opportunities for family-based physical activities. Given this situation, family-based physical activity programs are appropriate for the Hong Kong context. This is important because there is an association between the activity levels of parents and their children [19], as well as their attitudes towards physical activity [26]. Thus, increasing activity levels of both children and their parents may result in sustained changes in both generations, increasing the long-term effectiveness of the intervention. Researchers have shown that interventions that used a family-based approach can be effective [27]. Nonetheless, not all physical activity programs involving parents’ participation were effective [28]. New interventions must build on, and extend the extant literature to maximize intervention effectiveness. For instance, most family-based interventions focused on mothers only. Morgan and colleagues [17, 29, 30] found that father-focused interventions were also effective. The findings suggest that both mothers and fathers might be important social agents who affect intervention effectiveness. Nonetheless, to our knowledge, none of these programs was strongly theory-driven. Empirical evidence relating to the effectiveness of these programs is also unavailable.

### Physical activity and self-determination theory

Based on self-determination theory (SDT) [31], the manner in which support is provided, whether being need-supportive or controlling, could lead to different motivational or behavioral outcomes. For instance, a need supportive parent acknowledges children’s feelings and perspectives and provides meaningful choices; whereas a controlling one, uses pressure or rewards to initiate behavior [32]. According to the tenets of SDT, adopting a need supportive parenting style will promote higher levels of basic need satisfaction of competence, autonomy, and relatedness, and in turn positive behavioral change, and psychological well-being [31, 33]. By contrast, controlling behaviors may lead to the frustration or undermining of these basic needs, which may, in turn, diminish children’s physical and psychological well-being [34, 35]. Although empirical studies have been conducted to examine the latter relation in other domains such as physical education [36] and parenting [37], it has not been examined in parent-child dyads within the context of physical activity.

The “Active 1 + FUN” family-based physical activity intervention program for children and parents was designed to increase activity behaviors and fundamental movement skills of children, and also their fathers and mothers. We also aim to examine the relation between parents’ interpersonal styles and their children’s need satisfaction/frustration, and in turn the impact on physical activity behaviors and well-being. Through the proposed intervention, we also aim to help parents become more need supportive, and less controlling. The intervention will draw on previous evidence (e.g., [29, 30, 38]), but will also be tailored based on the sociocultural background of the Hong Kong context to enhance effectiveness. Specifically, children and parents who participate in the intervention will be invited to interactive workshops and activity sessions. Inexpensive and widely available sports equipment (e.g., skipping ropes, soft volleyballs, sponge flying discs) will be used during activity classes, and given to participants as gifts to encourage physical activity outside intervention classes. Interactive workshops will be provided to parents and children on topics such as healthy lifestyles, time management and parenting practices based on the tenets of SDT. One of the workshop goals is to provide a platform for parents to listen to children’s feelings about physical activity and provide suggestions on how parents can address children’s perspectives in a supportive way. Activity planning consultation, the parent-child physical activities homework and the available online materials will allow the participants to have a thorough understanding towards FMS and to set goals according to their abilities alongside to boost their physical activity level.

The effectiveness of the intervention will be evaluated using a randomized controlled trial. Eligible children and their parents will be randomly assigned to the experimental group or a wait-list control group. Quantitative measures will be taken at baseline, at the end of intervention period (accelerometer measure will be taken during a period that included the day of the tenth intervention session, secondary outcomes will be taken the week immediately before the session) and post-intervention follow-up (one year after baseline), for all children and their parents who took part in the intervention. The primary outcome of the trial will be time children’s spent in leisure-time MVPA, measured objectively using accelerometers.

### Objectives and hypotheses

The main objective of the current trial is to evaluate the effectiveness of a family-based physical activity intervention regarding changes in the objective measurement of the physical activity behaviors of parents and their children. We will also investigate the potential mediating effects of perceived parental autonomy support and controlling behaviors on children’s psychological need satisfaction or thwarting, and in turn their activity behaviors. Furthermore, we will examine how the intervention was perceived by the participants and whether it successfully initiated behavior changes through qualitative interviews. We hypothesize that relative to children and parents in the control group, participants in the experimental group will show significantly greater increases in MVPA from baseline to both post-intervention time points. We also hypothesize that children in the experimental group will report higher levels of perceived parental autonomy support, and lower parental controlling behaviors, when compared to their control group counterparts. Potential mediation effects of needs satisfaction and motivation on behavioral and health outcomes will be examined using structural equation modelling methods.

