The intervention also includes multiple components associated with specific behavior change strategies [40], and target specific theoretical constructs (see Table 1). The main intervention period will last for approximately 6 months, the length of intervention may vary among participating schools because of the differences of their academic calendars (exam periods, public or school holidays, and school activities would be avoided during the intervention to minimize disturbances to regular school activities). Participants will attend ten biweekly 90-min intervention sessions. Each session will consist of two parts, a 30-min interactive workshop followed by a 60-min activity session. An additional booster session will be provided approximately three months after the tenth intervention session. Both fathers and mothers will be invited to the intervention sessions, and at least one parent must be present during each intervention session.

**Table 1 Tab1:** List of intervention components and associated dosage, behavior change strategies, and hypothesized mediators

Intervention components	Dose	Description	Behavior Change techniques using Michie et al.’s [40] taxonomy	Hypothesized mediators
1. Interactive workshop	Ten 30-min biweekly sessions	Storytelling will be the critical teaching strategy for the workshops. There will be different stories and themes for each of the workshop; for instance, the key concepts of SDT and the ‘SAAFE’ teaching principle, the importance and benefits of the routinizing physical activity. A strong focus will be on ways to increase parent’s need support and reduce controlling behaviors, in which the differences between supportive and controlling behaviors will be illustrated with real-life examples.	- Goals and planning - Feedback and monitoring - Social support - Shaping knowledge - Natural consequences - Repetition and substitution - Identity	- Need support/ controlling behaviors - Competence - Autonomy - Relatedness - Autonomous motivation
2. Activity session	Ten 60-min biweekly sessions	Parents and children will attend activity sessions together. Sessions include rough and tumble play, and FMS training.	- Feedback and monitoring - Social support - Shaping knowledge - Comparison of behavior - Repetition and substitution	- Need support/ controlling behaviors - Competence - Autonomy - Relatedness - Autonomous motivation

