### Primary and secondary outcomes of the trial

The primary outcome of the randomized controlled trial is children’s MVPA. Parents’ MVPA and the time parents and children spend doing activity together (co-physical activity) will be measured as secondary outcomes. Other secondary outcomes of the trial include (i) parents’ and children’s FMS competency, (ii) parents’ and children’s BMI, (iii) children’s perceived need support and control, (iv) parents’ provision of need support and psychological control, (v) children’s and parent’s basic psychological needs satisfaction and thwarting, (vi) parents’ motivation towards physical activity, (vii) children’s and parent’s well-being.

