#### Basic psychological needs satisfaction and frustration – Children and parents

The satisfaction and frustration of three basic psychological needs of autonomy, competence, and relatedness have essential consequences for one’s physical and psychological health [33]. Children and parents’ perceived basic need satisfaction and frustration will be measured using a scale adapted from Ng, Ntoumanis, Thøgersen-Ntoumani, Stott, and Hindle [53]. The 18-item scale measures the facets of perceived basic need satisfaction or furstration towards physical activity participation; for instance, “People I know tell me I am good at sports” (competence satisfaction), “I feel free to choose what to do” (autonomy satisfaction), “people around me care for me” (relatedness satisfaction), “I encountered situations where I was made to be incompetent” (competence frustration), “I feel forced to follow decisions made for me” (autonomy frustration), and “I feel others dislike me” (relatedness frustration). Respondents will make responses using a 7-point scale from 1 (“Strongly disagree”) to 7 (“Strongly agree”).

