### Statistical methods

Data analyses will be conducted using linear mixed models using an intention-to-treat approach. Group differences concerning all primary and secondary outcomes will be examined. Specifically, a two-level (i.e., level 1 = time, level 2 = individual) model will be examined for each outcome, using the equation: Outcome = B_0_ + B_1_*Time + B_2_*Group + B_3_*Time*Group. The B_1_ coefficient will be parameterized as a variable with random slope and random intercept at all levels. Additional analyses will be conducted by adding the potential covariates and mediators to the models. An intervention effect will be deemed to be present if the B_3_ coefficient was statistically significant from zero.

Structural equation modelling will also be used to test the structural model of children’s perceived need support/control predicting need satisfaction/thwarting, and in turn physical activity behaviors and well-being. In the same model, we will examine the relationship between parents’ self-reported need supportive/controlling behaviors and children’s perception of the same constructs. Based on the work of Radel, Sarrazin, Legrain, and Wild [56], we will also examine the link between parents’ need satisfaction and their parenting styles in the model. To account for the relatively small sample size, a Bayesian approach will be used for structural equation modelling analyses (e.g., [53]).

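### Motivation is named as a mediator but has no path in the structural equation model and no child measure, and that model has no term for randomized arm

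*Protocol article*

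**What the plan says.** The protocol article deals with mediation in four places.

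- **Objectives and hypotheses** gives two mediation aims. The first concerns the "potential mediating effects of perceived parental autonomy support and controlling behaviors on children’s psychological need satisfaction or thwarting, and in turn their activity behaviors". The second reads: "Potential mediation effects of needs satisfaction and motivation on behavioral and health outcomes will be examined using structural equation modelling methods".
- **Intervention, Table 1** has a column of hypothesized mediators for each intervention component. "Autonomous motivation" appears there for the interactive workshop and for the activity session.
- **Primary and secondary outcomes of the trial** lists "v) children’s and parent’s basic psychological needs satisfaction and thwarting" for both generations, but for motivation only "vi) parents’ motivation towards physical activity, (vii) children’s and parent’s well-being".
- **Statistical methods** gives a mixed model with Time, Group and Time × Group for every outcome, and says that covariates and mediators may be added to it. Then: "Structural equation modelling will also be used to test the structural model". The paths named are from children's perceived need support or control to their need satisfaction or thwarting, and on to activity and well-being. Two parental links are added: from parents' self-reported behaviors to children's perceptions, and between parents' need satisfaction and their parenting style.

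**The concern.** The four places do not agree on motivation. The objectives assign it to structural equation modelling, Table 1 makes it a mediator of two components, the outcome list restricts it to parents, and the structural model leaves it out. An analyst following Statistical methods would not produce the result that the objectives promise.

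The structural model also lacks the one variable that was randomized. Table 1 presents its mediators as routes by which the intervention components act, so the cause of interest is allocation. A model that starts from children's perceived support describes how reports and activity go together. A family that reports more support and more activity may do so for reasons unrelated to the program. Without arm in the model, a good fit could be read as evidence of how the intervention works when it shows only that the constructs are associated.

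**Working it through.** No arithmetic bears on this point. The only computed figure in the plan is the sample size, which reproduces: 64 per arm, or 128, for d = 0.5 at two-sided 0.05 and 80% power, then 128 / (0.7 × 0.9) = 203.2, rounded up to 204. It is set for children's MVPA at 6 months and does not depend on the mediation analyses. The check is a comparison of sections.

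**Step 1. Match each named construct to an outcome, a measure and a model.**

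| Construct | Listed as outcome | Measure described | In the structural model | In the mixed models |
|---|---|---|---|---|
| Need support / control | Children and parents | Yes, both | Yes | Yes, as outcomes |
| Needs satisfaction / thwarting | Children and parents | Yes ("The 18-item scale measures the facets of perceived basic need satisfaction") | Yes | Yes, as outcomes |
| Motivation | Parents only | None | No | Parents' only, as an outcome |
| Randomized arm | not applicable | not applicable | Not named | Yes (Group, Time × Group) |

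Motivation is the only listed outcome without a measurement description. MVPA, co-physical activity, movement skills, BMI, perceived support and control, parental provision, needs and well-being all have one.

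**Step 2. Try both readings of motivation.** The objectives do not say whose motivation is meant.

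- If children's: it is not an outcome, has no measure and has no path.
- If parents': it is an outcome, but has no described measure and no path in the model to which the objectives assign the test.

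The sections conflict on either reading.

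**Step 3. Ask what would give mediation of the randomized effect.** Write *a* for the effect of arm on a mediator and *b* for the effect of that mediator on the outcome with arm in the model. The indirect effect of arm is *a* × *b*.

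- *Structural model as described*: support/control → needs → activity and well-being. Arm is not a node, so there is no *a* and no product.
- *Mixed model on each mediator*: mediator = B0 + B1·Time + B2·Group + B3·Time·Group. B3 supplies *a* for need support/control and needs, since these are secondary outcomes.
- *Mixed model on activity with mediators added*: this gives a mediator coefficient with Group in the model, a candidate for *b*. It also changes the meaning of B3, which becomes conditional on variables measured after randomization.

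The pieces for *a*, and arguably for *b*, are therefore scattered over separate models. No stated analysis combines them into an indirect effect of arm.

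**The case against.** The strongest reply is that the structural model matches its principal aim. That aim is a chain from perceived parental support and control through children's needs to activity. Each link is measured at all three times and the model tests that chain. The aim does not mention an indirect effect of allocation. This stands. A reader might infer that none of the mediation hypotheses can be tested, and the article does not support that.

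Second, arm is not absent from the mediator analyses. Group differences on need support, control and needs are tested through Time × Group, and mediators may be added to models that contain Group. This also stands, and it rules out saying that arm is ignored for every mediator. What remains is that these parts are never joined into an indirect effect.

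Third, a reader might take the structural model to exclude baseline values. The article is silent on waves and covariates in that model, which a condensed article may leave to the full plan. Silence is not exclusion, so no fault is claimed here.

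Fourth, the article never says that children's motivation is the mediator. The child reading is natural, because the sentence follows a hypothesis about children and the primary outcome is children's MVPA, but it is an inference. The missing scale could by itself be condensation. The disagreement among the objectives, Table 1, the outcome list and the model paths could not.

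Finally, entering arm does not make the mediator-to-outcome step randomized. That is correct and limits what the fix can deliver.

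**Conclusion.** The concern holds in a limited form. As written, mediation by motivation cannot be estimated in the structural equation model, and for children it cannot be estimated at all, because their motivation is neither a listed outcome nor given a described measure. The structural model has no arm term, so it estimates associations along its chain and does not show whether the intervention acts through the mediators in Table 1.

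The size is qualitative: one named mediator without an analysis path, and no stated indirect effect of arm. The chain linking support, needs and activity remains testable, and the primary outcome, its Time × Group test and the sample size are untouched. The change is worth making because mediation is a stated objective that the Discussion repeats, but it is secondary to the main comparison.

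The conclusion assumes that the paths listed under Statistical methods are the model intended. If a fuller analysis plan already includes arm and motivation, the article's text needs only to be aligned with it.

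**What to change.** 1. **Arm in the structural model.** Enter randomized arm as an exogenous predictor of the post-baseline mediators and of the outcome. Adjust mediators and outcome for the baseline values already collected. Report the indirect effects of arm with intervals (credible intervals under the planned Bayesian approach). State which waves supply mediator and outcome; the choice of wave is the sponsor's. Say plainly that the mediator-to-outcome path remains observational.
2. **Motivation.** Reconcile Objectives and hypotheses, Table 1, the list of secondary outcomes and Statistical methods. Either state whose motivation is meant, the scale, and its path in the model, or delete motivation from the mediation objective and from Table 1.

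The first change costs only analysis-plan wording, as the data are already scheduled. The second costs the removal of one claim or, if children's motivation is kept, a few questionnaire items per child at each wave.
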